##### 2.3.4.3 Alcohol consumption and smoking habits

Standardised questionnaires will be used to evaluate the consumption of alcohol and smoking habits. The latter will be assessed through a questionnaire with four standard questions adapted from the MONICA study conducted by the WHO (The World Health Organization MONICA, 1988). The participants of the study will be classified as current smokers or non-smokers (if they have never smoked or have not smoked in the last year). To evaluate the consumption of alcohol, we will employ a structured questionnaire that will assess the intake of alcoholic beverages in the previous week, estimating the grams/week consumed, and classifying the patients in the following categories according to the criteria of the Spanish Health Ministry: teetotaller, low risk, intermediate risk, and risk consumption (Sanidad Md: Límites de Consumo de Bajo Riesgo de Alcohol, 2020).

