The alteration in the structure of the vascular wall evaluated with carotid artery ultrasound and ankle-brachial index (ABI) along with AS have been used as biomarkers to improve the prediction of cardiovascular risk (Visseren et al., 2021). AS presents with a decrease of artery elasticity, and it is a predictor of risk of cardiovascular diseases of similar or greater importance with respect to other traditional cardiovascular risk factors (Visseren et al., 2021). Thus, AS measured in a non-invasive manner, with carotid femoral pulse wave velocity (cfPWV), brachial-ankle pulse wave velocity (baPWV), and cardio-ankle vascular index (CAVI), has shown a positive association with cardiovascular events (Ohkuma et al., 2017; Zhong et al., 2018; Matsushita et al., 2019; Miyoshi et al., 2021; Yasuharu et al., 2021). AS is mainly determined by age, sex and arterial pressure (Laurent et al., 2019; Visseren et al., 2021). In this way, when the central arteries become more rigid, they maintain their duct functions, although they progressively lose their storage properties (Williams et al., 2018a). AS is related to cardiovascular risk factors, lifestyles, inflammatory factors, and psychological factors (Avolio, 2013; Tsai and Hsu, 2021). Therefore, its detection can play an important role in the prevention of cardiovascular diseases, as its alteration appears before the vascular structure is affected (Williams et al., 2018a). Currently, we can measure vascular structure and function in a non-invasive manner. cfPWV, measured with tonometry, is considered the measure of reference (Williams et al., 2018a). cfPWV depends on the arterial pressure at the time of the measurement, and it reflects the AS of the descending aorta, iliac arteries, the first portion of the femoral arteries, the brachiocephalic trunk, and the common carotid artery, without evaluating the ascending aorta, and it is a measure of central AS (Boutouyrie and Vermeersch, 2010). baPWV, measured by oscillometry, is a measure of peripheral AS (Munakata, 2016). CAVI, also evaluated through oscillometry, analyses the stiffness of the aorta (including the ascending aorta) and the iliac, femoral and tibial arteries; it does not depend on the arterial pressure at the time of the measurement, and it is considered a measure of both central and peripheral AS (Shirai et al., 2011; Namba et al., 2019). AS is associated with the appearance of vascular ageing (Nowak et al., 2018; Laurent et al., 2019), reflecting the dissociation between the chronological and biological age of the major arteries, with their alteration preceding the appearance of cardiovascular events (Williams et al., 2018a; Nowak et al., 2018; Laurent et al., 2019). Vascular ageing is used for the early identification of subjects that could benefit from primary prevention. It is described as a gradual process that involves biochemical, enzymatic and cellular processes in the vascular area combined with epigenetic and molecular alterations, and it is considered that it is a fundamental reflection of biological ageing in general, and a determinant of vascular functioning (Mikael et al., 2017; Nowak et al., 2018). During the last decades, epidemiological studies have been conducted to unravel the determining factors of vascular ageing, drawing great interest, as it shows a stronger relationship with morbimortality by cardiovascular diseases than biological ageing (Nowak et al., 2018; Laurent et al., 2019). In this sense, it is known that early vascular ageing (EVA), normal vascular ageing (NVA) and healthy vascular ageing (HVA) are related to the progression of the deleterious characteristics of arterial functioning, which is influenced by the genetic background, the prevalence of classic cardiovascular risk factors, lifestyles and inflammatory factors (Niiranen et al., 2017; Botto et al., 2018; Ji et al., 2018; Nilsson et al., 2018; Nowak et al., 2018; Foscolou et al., 2019). The effect of physical activity on vascular ageing has been analysed in numerous studies, confirming that it plays an important role by mitigating vascular ageing, increasing the availability of nitric oxide (NO) and reducing oxidative stress and vascular wall inflammation (Andersson et al., 2015; Antunes et al., 2016; Jakovljevic, 2018; Zhang et al., 2018; Kucharska-Newton et al., 2019; Gomez-Sanchez et al., 2020). However, some authors suggest that this effect is different between sexes (Seals et al., 2019) and varies depending on the type of physical activity performed (Li et al., 2015). The benefits of the Mediterranean diet (Martinez-Gonzalez et al., 2019; Papadaki et al., 2020; Liu et al., 2021; Morze et al., 2021) and the influence of smoking habits and alcohol consumption on cardiovascular diseases (Kondo et al., 2019; Gonzalez-Sanchez et al., 2020) is widely demonstrated. Lastly, the psychological factors can worsen the inflammatory response or increase the blood levels of cortisol (Shah et al., 2011). Thus, different psychological components such as anxiety, depression and chronic stress can enhance vascular ageing. Nevertheless, the relationship among the determining factors of vascular ageing continues to be an area of interest for research (Gomez-Sanchez et al., 2022). Therefore, maintaining a process of NVA is fundamental for preserving vascular health and delaying the appearance of cardiovascular diseases (Mikael et al., 2017; Nowak et al., 2018). Currently, there is no consensus on a definition of vascular ageing. In this regard, several authors have defined HVA, excluding hypertensive or diabetic subjects from the group of HVA (Niiranen et al., 2017; Ji et al., 2018; Nilsson et al., 2018), and using the percentiles of cfPWV below 10 or 25 from a reference population, or from their own study population, stratified by age groups, and some authors also take into account the values of arterial pressure. Different definitions of EVA have also been published (Van Bortel et al., 2012; Cunha et al., 2015; Cunha et al., 2017; Botto et al., 2018), which are gathered in several studies that consider the highest percentiles of cfPWV for its definition. Various works have employed the values published by Boutouyrie et al. in a European population as reference values (Boutouyrie and Vermeersch, 2010). Our research group has recently published reference values of the different measures of AS for the Spanish adult population without previous cardiovascular disease (Gómez-Sánchez et al., 2020a). Furthermore, we have analysed AS in a general population without cardiovascular disease, measured with several parameters and using different criteria of vascular ageing, analysing their relationship with lifestyles, cardiovascular risk factors, inflammatory factors and psychological factors (Gómez-Sánchez et al., 2020b; Gomez-Sanchez et al., 2020; GómezSánchez et al., 2020). Therefore, we consider that the best definition of vascular ageing must be that which considers the following variables: age, arterial pressure and sex (i.e., the variables with greatest influence on AS), as well as the percentiles of cfPWV of the study population.

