
To sum up, persistent COVID may affect the entire spectrum of COVID-19 patients, from those with a very mild acute disease to those who are seriously ill. The symptoms are heterogeneous, including fatigue, post-effort discomfort, dyspnea, cognitive deterioration, sleep disorders, anxiety and depression, muscle pain, brain fog, anosmia/dysgeusia, headache and limitation of the functional capacity, which affect the quality of life of the patients. The relationship between AS and vascular ageing is not clear. The starting hypothesis of this study states that individuals diagnosed with persistent COVID present greater alteration in the vascular structure and function, as well as worse vascular ageing, compared to the general population without a diagnosis of persistent COVID, since the vascular system of these people is subjected to complex inflammatory deregulation, which has not been studied to date.

Therefore, the main objectives of this study are: 1) to analyse vascular structure, vascular function, biomarkers of endothelial damage and ageing in Spanish adults diagnosed with persistent COVID, determining the differences between sexes; and 2) to analyse the association of the clinical symptoms, lifestyles (physical activity, diet, alcohol consumption and smoking habits), and psychological, cognitive and inflammatory factors with biomarkers of endothelial damage, vascular structure, function and ageing, determining the differences by sexes. Regarding the secondary objectives of this study, we will analyse the possible differences among individuals with persistent COVID according to whether the infection is caused by the Delta mutation or the Omicron mutation. Furthermore, in order to continue advancing in the recognition and visibility of the patients affected by persistent COVID, they will be given a voice through a focal discussion group, where we will delve into the opinions and experiences of the population to facilitate the transfer of the study to the habitual clinical practice.

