### 2.2 Study population

Through consecutive sampling, we will select 300 subjects who meet the clinical definition of persistent COVID of the WHO, established by international Delphi consensus, along with patients, their representatives, and experts from the five continents. Persistent COVID is the condition that occurs in individuals with a history of probable or confirmed SARS-CoV-2 infection, generally three months after the onset of the disease, with symptoms that last for at least two months and cannot be explained by an alternative diagnosis. The common symptoms include, among others, fatigue, difficulty in breathing and cognitive dysfunction, and they generally have an impact on daily functioning. They can be de novo after the initial recovery from an acute episode of COVID-19 or persist from the initial disease, and they can also fluctuate or relapse over time (Soriano et al., 2022). The exclusion criteria of the study will be: terminal subjects, subjects who cannot go to the health centres, subjects with a history of cardiovascular disease (ischemic heart disease or cerebrovascular disease) and glomerular filtration rate below 30%. The individuals will be recruited from the registries of the Primary Care offices and the Persistent COVID Office of Internal Medicine in the health area of Salamanca. The sample size was calculated using the GRANMO free software (http://www.imim.cat/ofertadeserveis/software-public/granmo/), detecting a difference in cf-PWV of 0.35 metres/second between subjects with persistent COVID and a sample of Spanish population without cardiovascular disease (Gómez-Sánchez et al., 2020a). Accepting an alpha risk of 0.05 and a beta risk below 0.2 in a bilateral contrast, and assuming a standard deviation of 2.1, a total of 283 individuals are required to detect the indicated difference as significant. Therefore, the 300 subjects that will be included in the study will be sufficient. The subjects included in the study are shown in Figure 1. The patients did not participate in the design of the study; however, they will participate actively in the recruitment, by disseminating the objectives of the study and the inclusion criteria through their organisations. By means of discussion groups, we will investigate the opinions and experiences of the study population about the influence of persistent COVID on vascular health. Similarly, their opinions and attitudes will be considered to facilitate the transfer to the clinical practice. At the end of the study, we will send a detailed report to each patient with the results of the tests conducted. Moreover, a dissemination session will be organised for all the patients included in the study.

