### 2.4 Statistical analysis

The data will be registered using the REDCap platform (Research Electronic Data Capture) (Harris et al., 2009; Harris et al., 2019) with a data-gathering questionnaire designed for the project. The normal distribution of the variables will be verified through the Kolmogorov-Smirnov test. The arterial stiffness variables will be standardized and expressed as Z scores to compare results with other reference populations. The analysis of the difference of means between variables of two categories will be performed through Student’s t-test or Mann-Whitney U-test, depending on each case, whereas the qualitative variables will be analysed through X^2^ test. To analyse the relationship between qualitative variables of more than two categories and quantitative variables, an analysis of variance (ANOVA) will be conducted, and a Bonferroni’s test will be performed for the post hoc analyses. The Kruskal-Wallis test will be applied in those cases in which the variables do not show a normal distribution. The analysis of covariance (ANCOVA) will be carried out to control for the variables that can be affected by the results as confounding factors. The relationship among quantitative variables will be analysed using Pearson’s or Spearman’s correlation, depending on each case. In the multivariate analysis, we will use multiple linear regression and logistic regression analyses, with the necessary adjustments according to the type of variables analysed. All variables will be analysed disaggregated by sex, and, whenever applicable, the differences will be analysed from a gender perspective, considering the known influence of gender on many pathologies, particularly cardiovascular and cerebrovascular diseases. The data will be analysed using the SPSS v28.0 statistical package for Windows (IBM, Armonk, New York: IBM Corp). Statistical significance will be set at p < 0.05.

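### Smoking is coded in two levels that pool former with never smokers. If former smokers keep some excess stiffness, this understates the current-versus-never difference, and a three-level coding would cost little.

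*Protocol article*

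**What the plan says.** Section 2.3.4.3 measures smoking with "a questionnaire with four standard questions adapted from the MONICA study". The four items are not printed. It then fixes the coding: "The participants of the study will be classified as current smokers or non-smokers", where the second group is "non-smokers (if they have never smoked or have not smoked in the last year"). By implication, people who stopped within the past year count as current smokers. No former-smoker level, cumulative exposure or time since stopping is described.

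Main objective 2 (section 1) relates several factors, among them "lifestyles (physical activity, diet, alcohol consumption and smoking habits"), to vascular structure, function and ageing and to endothelial biomarkers. The same section treats as established "the influence of smoking habits and alcohol consumption on cardiovascular diseases", and it describes vascular ageing as gradual.

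For confounding, section 2.4 says: "The analysis of covariance (ANCOVA) will be carried out to control for the variables that can be affected by the results as confounding factors". For the multivariable work it says: "we will use multiple linear regression and logistic regression analyses, with the necessary adjustments according to the type of variables analysed". No covariate is named.

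**The concern.** The outcomes include carotid intima-media thickness, plaque, pulse wave velocity and vascular ageing class. By the protocol's own account, vascular ageing develops over time, yet the smoking variable looks back only one year. Long-term smokers who stopped more than a year ago enter the comparison group. If they still carry some excess, they raise the mean of the group labelled non-smokers and narrow the observed contrast.

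Two results are at stake. One is the smoking association itself, which is part of a main objective. The other is any association adjusted for smoking with this variable, because differences between former and never smokers would stay uncontrolled. Alcohol, in the same section, gets four categories, so finer grading of a lifestyle factor is already part of the study's practice.

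**Working it through.** **The plan's own figure.** The only sample size given (section 2.2) uses a difference of 0.35 m/s, SD 2.1 m/s, two-sided alpha 0.05 and power 80%. A one-sample normal approximation gives n = (2.1 × 2.8016 / 0.35)² = 282.56, rounded up to the stated 283. It concerns persistent COVID against a reference population. It does not involve smoking, so the coding rule leaves it untouched. From that section I use only SD 2.1 and N = 300.

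**Attenuation.** Let c, f and v be the proportions of current, former (more than one year) and never smokers. Let D be the true current-versus-never difference and g the fraction of D that former smokers retain.

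- The pooled non-smoker mean lies above the never-smoker mean by g × D × f/(f + v).
- The two-level contrast is therefore D × [1 − g × f/(1 − c)], and the attenuation is g × f/(1 − c).

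The article gives none of c, f, g or D, so all four are assumptions. With c = 20%:

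| f | g | Attenuation |
|---|---|---|
| any | 0 | 0% |
| 20% | 0.25 | 0.25 × 0.20/0.80 = 6% |
| 30% | 0.50 | 0.50 × 0.30/0.80 = 19% |
| 40% | 0.75 | 0.75 × 0.40/0.80 = 38% |

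Varying c from 15% to 25% with the same f, the two-level contrast recovers 87–94% of D at g = 0.25, 73–88% at g = 0.5, 60–82% at g = 0.75, and 100% at g = 0.

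**Incomplete adjustment.** Give never, former and current smokers the scores 0, g and 1, and ask how much of the score's variance the two-level variable misses. For c = 20%, f = 30%, g = 0.5:

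- Mean score = 0.20 + 0.15 = 0.35; total variance = 0.20 + 0.30 × 0.25 − 0.35² = 0.1525.
- Non-smoker mean = 0.15/0.80 = 0.1875; variance captured = 0.20 × 0.80 × (1 − 0.1875)² = 0.1056.
- Share missed = 1 − 0.1056/0.1525 = 31%.

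With c from 15% to 25% and f from 20% to 40%, the share missed is about 5–12% at g = 0.25, 21–42% at g = 0.5 and 41–69% at g = 0.75. It is zero at g = 0. This applies only to models that use the two-level variable as the smoking term.

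**Power.** Take N = 300, SD 2.1, c = 15% (45 people), f = 30% (90), v = 55% (165), D = 1.0 m/s and g = 0.5.

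- Two levels: expected contrast 1.0 × (1 − 0.5 × 0.30/0.85) = 0.82 m/s. SE = 2.1 × √(1/45 + 1/255) = 0.340. Power is 68%.
- Three levels, current versus never tested alone at 0.05: expected contrast 1.0 m/s. SE = 2.1 × √(1/45 + 1/165) = 0.353. Power is 81%.
- Three levels, three Bonferroni-corrected pairwise comparisons (alpha 0.05/3, critical value 2.394): 1.0/0.353 − 2.394 = 0.44. Power is 67%.

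Section 2.4 plans Bonferroni post hoc tests for variables with more than two categories. On that footing the comparison in this example is 67% against 68%. The three-level figure stays at 67% whatever g is, while the two-level figure is 77% at g = 0.25 and 58% at g = 0.75.

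**The case against.** The rule is explicit and reproducible, and nothing in the article contradicts it. Four further objections deserve weight.

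- **The target is not stated.** Objective 2 speaks of smoking habits, not of current versus never smoking. As a contrast of smoking against not smoking in the last year, the two-level estimate is not biased; it answers a narrower question. This stands. A reader might infer that the rule always yields a biased estimate, but the text supports only the conditional statement.
- **The questionnaire items are not shown.** A reader might infer that former smoking is recorded and then thrown away. The wording of the rule suggests that past smoking is asked about. It does not prove it, since one question on smoking in the last year would be enough to apply the rule. Nor does a classification delete the recorded answers.
- **No covariates are named.** A reader might infer that the adjusted analyses are already confounded by smoking. Section 2.4 does not say that smoking is a covariate or that this variable would be the model term. Incomplete adjustment follows only for models that use it.
- **Splitting costs precision.** With 15% to 20% current smokers there are 45 to 60 of them before the planned analyses by sex. After Bonferroni correction the power advantage disappears in the middle case and reverses when former smokers retain little. This also stands.

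These points limit the size and certainty of the concern. They do not supply a reason to pool the groups where the outcome is gradual vascular change.

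**Conclusion.** The point holds in conditional form. The article fixes a two-level smoking variable that treats people abstinent for more than a year as never smokers, in a study where smoking habits are an exposure in a main objective. If former smokers retain part of the excess, the contrast understates the current-versus-never difference, and adjustment through this variable is incomplete.

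The size cannot be taken from the document. Under the assumptions shown with 20% current smokers, attenuation is 0% to 38%, and 19% in the middle case. The zero end, where former smokers match never smokers, is a genuine possibility. The case for change rests on bias and interpretability, not on power. Severity is minor.

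**What to change.** Code smoking as never, former and current. Use the three levels as the exposure in objective 2 and wherever smoking is a covariate. Take the levels from the existing questionnaire if it records past smoking; otherwise add one question. Keep the two-level version for comparison with reference datasets that offer nothing finer, and describe it there as smoking versus not smoking in the last year.

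The cost is a recode or one extra question, and one extra degree of freedom. Groups become smaller, especially by sex, and power is not assured to rise if all three pairwise comparisons are Bonferroni-corrected. Recruitment, vascular measurements and the planned 300 participants do not change.

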#### 2.3.5 Vascular structure

Vascular structure will be evaluated using a Sonosite Micromax ultrasound device (FUJIFILM Sonosite, Washington, USA), measuring the carotid intima-media thickness (cIMT), using a high-resolution, 5-10 Mhz multifrequency, lineal transducer and the Sonocal software, which makes automatic measurements of cIMT to optimise the reproducibility (Gómez-Marcos et al., 2012). The carotid ultrasound will be carried out by researchers who will be trained for this purpose before the beginning of the study. Common carotid measurements will be performed after the examination of a 10 mm longitudinal section at 1 cm from the fork. Measurements will be made in the proximal wall and in the distal wall in the lateral, anterior and posterior projection, following an axis perpendicular to the artery in order to discriminate between two lines: one for the lumen-intima interface and the other for the media-adventitia interface. The measurements will be obtained with the patient lying down, head extended and slightly tilted opposite to the examined carotid artery. Pathological thickening of the intima media will be considered for cIMT > 0.9 mm, atheromatous plaque diameter over 1.5 mm, or focal increase of 0.5 mm or 50% of adjacent IMT (Williams et al., 2018b). ABI will be measured using a VaSera VS-2000® device (Fukuda Denshi Co, Ltd, Tokyo, Japan).

